#### Phase II: Adapt and Train

##### German Version of the Harvard Digital Navigator Training

Three researchers from the study team participated in a multiday training and coaching program on the implementation of DNs during field visits at Harvard Medical School [64]. Furthermore, the content of the certified HDNT was translated into German and adapted to the German context based on the findings from the focus groups and interviews. Depending on the results of the qualitative data (eg, information about the skills that are particularly important for DNs), the HDNT was adapted. If necessary, new modules were developed and added. Additionally, there was a participatory process in terms of a modified Delphi study [65] that involved patients (N=9) and HCPs (N=17) in discussion groups at three time points, following the levels of the European Commission’s Digital Competence Framework for Citizens (DigComp 2.0) [66]. During these discussion groups, selected components of the HDNT were presented and evaluated for their suitability in the German context. The content of the conversation was documented by a member of the study team in the form of field notes, which were subsequently presented to the entire study team and discussed within the team. Based on these insights, the study team developed an adapted version of the HDNT and designed the training sessions for the German DNs.

##### Training the Digital Navigators

Subsequently, clinical staff (preferably medical assistants who participated in phase II; n=6, 35.3%) were trained with the adapted HDNT as DNs in three training sessions. Each session lasted for 3 hours and took place over 3 consecutive weeks. The first session was held in person at the study site in Rüdersdorf. The following two sessions were web based. According to the predefined roles of DNs, the training entailed general knowledge about existing DiGAs and how to keep the knowledge of available DiGAs up to date. The DNs were provided with a study smartphone and a test account for each of the mental health DiGAs available. As part of the training sessions, all DiGAs available at the time of training were introduced and tested together, ensuring that all DNs could become familiar with the DiGAs, both theoretically and practically. This process enabled the DNs to gain a comprehensive overview of all available DiGAs, thus allowing them to recommend the most suitable one later. Additionally, technical issues and difficulties could be identified and resolved immediately.

Beyond the knowledge about the DiGAs, the DNs also received mental disorder–specific training. Currently, DiGAs are available for the following mental illnesses: anxiety disorders, depression, and eating disorders. The DNs were provided with an overview of the diagnosis, prevalence, and treatment of these mental illnesses. The main sources were the *International Classification of Diseases and Related Health Problems, 10th Revision* (ICD-10) [67] for diagnosis and the Association of Scientific Medical Societies (AWMF) level S3 treatment guidelines for mental illnesses [68]. This contributed to raising awareness and knowledge of mental health disorders, particularly among DNs working in GP settings, enabling them to assess these disorders competently.

Furthermore, DNs were instructed on how to deliver training on DiGAs to their multiprofessional teams in their workplace and how to use and process data generated by patients by using the DiGAs. Additional training content entailed recruitment of participants, technological troubleshooting, or the conduction of motivational check-in appointments with participants.

A key reference for DNs was the DIGAnavigator website, which we will develop based on the model of MindApps, the platform created by Harvard University. This new website will focus on integrating and evaluating German DiGAs. Initially, all DiGAs for mental health approved by the BfArM [38] in Germany will be listed on the website. In addition, detailed psychoeducational content on the use of DiGAs for mental health conditions will be developed and incorporated into the website.

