**Methods:**

This mixed methods study took place at six study sites (three psychiatric outpatient clinics, three general practices) in Germany. In the prestudy, patients and HCPs participated in semistructured interviews and focus groups concerning their acceptance and expectations of DNs (phase I). The Harvard Digital Navigator Training (HDNT) was adapted, and medical assistants were trained as DNs (phase II). During the intervention, 8 patients per site (N=48) diagnosed with a mental disorder were recruited via convenience sampling and supported by DNs in using DTx for mental health for 12 weeks (phase III). Patients’ (N=48) and HCPs’ (N=18) digital health literacy, digital and technical literacy, readiness and ability to change, and clinical symptom severity were assessed before and after 12 weeks of DTx prescription and support by DNs. Patient engagement with the DiGAs (usage duration and intensity) was measured after the intervention. Quantitative data were analyzed using a pre-post design. Finally, qualitative interviews were conducted with HCPs, patients, and DNs to explore their experiences with DNs, including perceived implementation barriers.

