In Germany, DTx are called *Digitale Gesundheitsanwendungen* (“digital health apps” [DiGAs]) and have been available since the implementation of the Digital Health Care Act (*Digitale-Versorgung-Gesetz*) in December 2019 [36]. This legislation established the framework for the approval and reimbursement of digital mental health apps. These apps must meet specific standards set by the German Federal Institute for Drugs and Medical Devices (BfArM) to ensure safety, quality, functionality, privacy, data security, and effectiveness [37]. Once approved, DiGAs can be prescribed by physicians and psychotherapists and are reimbursed by statutory health insurances. Currently, there are 72 DiGAs available, of whom 29 (40.28%) focus on mental health conditions (eg, n=7, 24.14% on depression; n=7, 24,14% on anxiety). All approved DiGAs can be found in the publicly available German DiGA directory of the BfArM [38].

Although DNs have been successfully implemented in several countries [11,32], no such role or training program currently exists in Germany. In addition, evidence from abroad cannot be easily transferred to Germany since the introduction of new roles, such as DNs, must align with existing structures, including statutory health insurance and professional licensing laws. As a result, the best practices from other countries must first be adapted to the German legal, financial, and organizational framework [39].

An exploratory pilot trial is therefore needed to gather preliminary information about the implementation of DNs in the German health care system and the feasibility of conducting a full-scale trial. The aim of this study is to (1) explore the acceptance and expectations of HCPs and patients in Germany toward DNs (2); adapt the Harvard Digital Navigator Training (HDNT) for the German health care system; (3) evaluate the trial implementation of DNs, including their impact on patients and other HCPs; and (4) investigate options for perpetuating DNs in the German health care system.

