### Eligibility Criteria for Patients

Patients provided written informed consent before any study procedures occurred (see Multimedia Appendix 2 for a sample informed consent form). Patients eligible for the trial had to comply with all the following inclusion and exclusion criteria listed in Textbox 1.

Inclusion and exclusion criteria for this study.Inclusion criteria:Diagnosis according to the
*International Classification of Diseases and Related Health Problems, 10th Revision*
(ICD-10) codes F01-F06.x or F06.7Ability to provide informed consentMinimum age of 18 yearsAbsence of significant cognitive deficits, as indicated by severe organic brain diseaseSufficient language skills to complete an interview in GermanSufficient modern hardware (eg, smartphone, tablet, or personal computer) availableBasic knowledge of how to use a smartphoneExclusion criteria:Ongoing or recent (≤3 weeks) qualified psychiatric or psychotherapeutic treatmentAcute danger to self or othersDisturbance of orientation or reference to realityDiagnosis of intellectual impairment

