#### Secondary Outcome Measures

As a secondary outcome measure, the severity of the patient’s disease was assessed and compared before and after the intervention using validated scales. This measure allowed for a comprehensive evaluation of the symptom burden, functional status, and overall clinical improvement.

The Global Assessment of Functioning (GAF) [56] and the Clinical Global Impression (CGI) [57] scales are brief clinician-rated tools that capture the clinician’s view of the patient’s overall functioning and treatment response and are widely used to evaluate symptom severity and improvement. To assess specific symptom domains, the following instruments were used: the Hamilton Anxiety Rating Scale (HAM-A) [58], which is an instrument that measures the severity of anxiety symptoms, and the Hamilton Depression Rating Scale (HDRS) [59], which evaluates depressive symptomatology across multiple dimensions, including mood, sleep, and somatic complaints. These clinician ratings were complemented by the Beck Depression Inventory-II (BDI-II) [60], a widely used self-report questionnaire that captures the patient’s subjective experience of depressive symptoms. Additionally, sleep quality was assessed using the Insomnia Severity Index (ISI) [61], a brief self-report measure that evaluates the nature, severity, and impact of insomnia, which often co-occurs with mental health conditions and may influence treatment outcomes.

Table 1 provides an overview of the instruments used for data collection and analysis. The specific methodological details for each study phase are described in the following sections.

**Table 1 table1:** Construct and data collection used for pre- and postassessment of the interventional study.

Outcome and participants		Construct	Data collection instrument

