#### Phase III: Pilot and Evaluate (Interventional Study)

In the intervention phase, the trained DNs trained the multiprofessional teams at the six study sites to select and integrate DiGAs for mental health into the treatment of 48 patients (n=8, 16.7%, per site). The DNs provided at least one training session for their teams. A guideline for this training was provided by the study team. Based on the findings from phases I and II, the content and structure of the intervention were finalized. It was established that selected patients would use a DiGA for 12 weeks and receive guidance and support from trained DNs during these 12 weeks, encouraging regular use of a DiGA tailored to their individual needs. To enhance adherence, participants were regularly asked about any challenges they encountered during check-up appointments with their DNs. To promote engagement, DNs suggested practical strategies, such as integrating DiGA use into daily routines or identifying suitable time frames for engagement. The study team supported the DNs through monthly web-based meetings. In these meetings, DNs received up-to-date information about the study progress, got an opportunity to ask questions, and exchanged experiences. During the intervention phase, DNs contacted the study team at any time if they had questions or encountered any issues. In addition, process data, such as the number and duration of contacts between patients and DNs, were collected during the intervention to enable the identification and validation of any qualitative differences in implementation at the different study sites.

The trained raters (n=6) conducted data collection with patients (N=48) and HCPs (N=18; n=3, 16.7%, per site) at each study site at two timepoints: before the 12-week intervention (preassessment), and directly after completing the intervention (postassessment). The end of the intervention phase was defined as the date of DiGA activation plus a 3-month DN support period. The study team also met with the raters once a month in a web-based meeting to discuss the progress of the preassessments and later postassessments. During these meetings, raters got an opportunity to ask questions and receive assistance with any issues or challenges they may have encountered.

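### The ICD-10 range printed as the diagnostic entry criterion does not cover the disorders the study's apps, training and outcome scales address, and is probably a misprint

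*Protocol article*

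**What the plan says.** The only diagnostic entry rule is the first inclusion item of Textbox 1, under Eligibility Criteria for Patients: an ICD-10 diagnosis with code F01-F06.x or F06.7. The criteria are cumulative: "Patients eligible for the trial had to comply with all the following inclusion and exclusion criteria listed in Textbox 1". A further inclusion item in the same box requires that the patient has no marked cognitive deficit of the kind seen in severe organic brain disease.

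Other sections describe the population and the intervention differently:

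- The Introduction counts 72 approved apps (DiGAs), "of whom 29 (40.28%) focus on mental health conditions". The examples it gives are "n=7, 24.14% on depression; n=7, 24,14% on anxiety".
- Training the Digital Navigators says: "Currently, DiGAs are available for the following mental illnesses: anxiety disorders, depression, and eating disorders". It continues: "The DNs were provided with an overview of the diagnosis, prevalence, and treatment of these mental illnesses". It names ICD-10 as the diagnostic source for that training.
- The Abstract (Methods) says "8 patients per site (N=48) diagnosed with a mental disorder were recruited via convenience sampling", without naming a diagnostic group.
- Phase III has the navigators "encouraging regular use of a DiGA tailored to their individual needs".
- Secondary Outcome Measures lists "the Hamilton Anxiety Rating Scale (HAM-A) [58], which is an instrument that measures the severity of anxiety symptoms", together with two depression scales (HDRS and BDI-II), an insomnia scale, and global ratings of functioning and severity.

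**The concern.** The diagnosis item decides who may enter phase III and what population the results describe. The printed codes do not match the conditions that the apps treat, that the navigators were taught about, or that the symptom scales measure. A site following the text literally would turn away a patient with primary depression, an anxiety disorder or an eating disorder. Those are the patients for whom the article says an app exists.

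If the sites used a different range, the published rule misdescribes the sample. Readers then cannot tell to whom the pre-post changes in literacy, engagement and symptom severity apply. Nor could the recruitment be repeated in the larger randomized trial that the Limitations section foresees.

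**Working it through.** No sample size, power or error rate is at stake, so the check is a comparison of texts.

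**Step 1: the code string by itself.** F06.x means every subcode of F06. F06.7 is one of them. The alternative after the word or therefore adds no patient. This can be seen from the text alone and suggests a drafting error in the string.

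**Step 2: what the range denotes.** The article does not define the codes, but the criterion names ICD-10 as its classification. In ICD-10, F01-F06 lies in the organic block: dementias, organic amnesic syndrome, delirium, and other mental disorders due to brain damage or physical disease. Primary depressive, anxiety and eating disorders are coded in other F groups.

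**Step 3: range against the rest of the article.**

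| Source | Conditions addressed | Inside F01-F06? |
|---|---|---|
| Training the Digital Navigators | anxiety disorders | No, for primary disorders |
| Training the Digital Navigators | depression | No, for primary disorders |
| Training the Digital Navigators | eating disorders | No |
| Introduction (examples) | depression, anxiety | No, for primary disorders |
| Secondary Outcome Measures | anxiety and depression scales | No, for primary disorders |

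The insomnia scale is left out of the table. The article presents sleep as a problem that accompanies mental illness, not as an entry diagnosis. No section names dementia or another organic disorder as a target, and none corrects or explains the range.

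**Step 4: range against the cognitive item.** Both items must be met. The cognitive item removes much of what the range admits, most directly the dementia codes. It does not remove everything. It is worded around severe organic brain disease, F06.7 (mild cognitive disorder) need not imply that, and F06 also contains organic mood and anxiety disorders. The two items fit awkwardly but can be met together.

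**Step 5: literal effect against reported enrolment.** Read literally, patients with the primary disorders in Step 3 are ineligible and few others qualify. The Results section nevertheless reports 48 enrolled by the end of March 2025, which meets the target of 6 sites × 8 patients = 48. Full recruitment in about four months makes it unlikely that the printed range was the one applied.

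**Step 6: the article's own figures.** 29/72 = 40.28% and 7/29 = 24.14% both reproduce. Neither bears on the code range.

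**The case against.** The strongest reply has four parts.

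**It is only a misprint in a condensed article.** Probably so. But condensation excuses what is left out, and this is an affirmative statement of the entry rule that is wrong as printed. Enrolment and intervention are over and the study claims feasibility rather than effectiveness, so a correction changes nothing about who entered. It still changes what readers understand the sample to be.

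**The meaning of the codes comes from outside the article.** This is partly right. Only the redundancy of F06.7 is visible in the text. The rest depends on the block structure of ICD-10. Since the criterion names that classification, the code meanings are part of the rule and not a recalled side source. The dependence should still be stated.

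**The cognitive item does not contradict the range.** This stands. A broad range narrowed by a second item is ordinary drafting, and some codes survive both. A reader might infer that the two items exclude each other; the wording does not support that.

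**The size cannot be measured.** This also stands. A reader might take 48 of 48 as the number of ineligible patients, but that is only the sample size. Likewise 7 + 7 = 14 of 29 might be read as the share of apps missed, but those counts are illustrative examples and the article does not say that the two groups are disjoint.

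**Conclusion.** The diagnostic criterion in Textbox 1 is wrong as printed. It is internally redundant and, on the ordinary meaning of ICD-10, it does not cover the primary anxiety, depressive and eating disorders on which the rest of the article is built. Applied literally, it makes the intended patients ineligible.

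The likely explanation is a misprint, inferred from the redundancy and from the completed enrolment. The article does not say so, and the range actually used cannot be recovered from it.

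A reader might go further and infer that the wrong patients were enrolled, or that an organic-disorder population was chosen on purpose. The document supports neither. It reports no enrolled patient's diagnosis, and every other description points to a general mental disorder population matched to a suitable app.

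The effect is on the description and reproducibility of the whole phase III sample. No number of misclassified patients can be given. The conclusion assumes that the codes carry their standard ICD-10 meaning and that no correction appears in a document not shown.

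**What to change.** - **Textbox 1.** Replace the printed range with the code list actually applied at screening. Reconcile it with the Introduction, Secondary Outcome Measures and Training the Digital Navigators. Name F06.7 separately only if it lies outside that list. No replacement range is proposed here; the sponsor must supply the one used.
- **Results report.** Tabulate the 48 patients by ICD-10 code and prescribed app, and report anyone outside the applied list as an eligibility deviation.

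The cost is one corrected line and one descriptive table, which should need only screening and prescription records already held. No analysis, sample size or study procedure changes.

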##### Training the Raters

In addition, 6 psychologists were trained as raters to conduct participant recruitment and data collection. The training session was conducted at the study site in Rüdersdorf and lasted 3 hours. During the training session, the raters learned more about the data collection process in the study. Specifically, they learned which instruments are used for pre- and postassessment, how data for self-assessment are collected, and what to consider when conducting an interview about the patients’ severity of disease. This training aimed to standardize testing and to promote consistency in data collection.

#### Phase III: Pilot and Evaluate (Interventional Study)

In the intervention phase, the trained DNs trained the multiprofessional teams at the six study sites to select and integrate DiGAs for mental health into the treatment of 48 patients (n=8, 16.7%, per site). The DNs provided at least one training session for their teams. A guideline for this training was provided by the study team. Based on the findings from phases I and II, the content and structure of the intervention were finalized. It was established that selected patients would use a DiGA for 12 weeks and receive guidance and support from trained DNs during these 12 weeks, encouraging regular use of a DiGA tailored to their individual needs. To enhance adherence, participants were regularly asked about any challenges they encountered during check-up appointments with their DNs. To promote engagement, DNs suggested practical strategies, such as integrating DiGA use into daily routines or identifying suitable time frames for engagement. The study team supported the DNs through monthly web-based meetings. In these meetings, DNs received up-to-date information about the study progress, got an opportunity to ask questions, and exchanged experiences. During the intervention phase, DNs contacted the study team at any time if they had questions or encountered any issues. In addition, process data, such as the number and duration of contacts between patients and DNs, were collected during the intervention to enable the identification and validation of any qualitative differences in implementation at the different study sites.

The trained raters (n=6) conducted data collection with patients (N=48) and HCPs (N=18; n=3, 16.7%, per site) at each study site at two timepoints: before the 12-week intervention (preassessment), and directly after completing the intervention (postassessment). The end of the intervention phase was defined as the date of DiGA activation plus a 3-month DN support period. The study team also met with the raters once a month in a web-based meeting to discuss the progress of the preassessments and later postassessments. During these meetings, raters got an opportunity to ask questions and receive assistance with any issues or challenges they may have encountered.

All patients and HCPs received an online self-assessment form (administered by the online survey service LimeSurvey), assessing sociodemographic parameters (eg, age, gender), digital health literacy, digital and technical literacy, readiness and ability to change, and severity of disease (see Table 1). Additionally, patients were interviewed on the severity of their disease and app engagement.

The collected sociodemographic characteristics were analyzed using descriptive statistics and presented in an appropriate format, such as age distribution and gender ratio. Quantitative primary data collected (eg digital health literacy, severity of disease) were analyzed using descriptive statistics in a pre-post comparison using paired *t*-tests or Wilcoxon signed-rank tests, depending on the distribution of the data. Effect sizes were reported to assess the magnitude of changes, and multiple linear regression models were used to control for potential confounders. Analyses were performed using SPSS with a statistical significance set at α=.05.

After the intervention, the study team conducted qualitative semistructured interviews and focus groups with 25 participants in total (n=13, 52%, patients; n=6, 12.5%, DNs; and n=6, 12.5%, HCPs) to assess the opportunities and implementation barriers to implementing DNs, as well as the effects of counseling and support by the DNs. The collected qualitative data were transcribed, pseudonymized, and analyzed using qualitative content analysis according to Kuckartz and Rädiker [69]. The diverse and complex narratives of the participants were recorded and explored using a multistage approach. The formation of categories and subcategories enabled the content of the information to be structured. The iterative procedure increased the comprehensibility of the information generated but also allowed flexibility and an interpretative approach. To ensure high-quality reporting, the COREQ (Consolidated Criteria for Reporting Qualitative Research) checklist (Multimedia Appendix 5) was followed [70].

